## Abstract

**Background:**

Alcohol is the leading psychoactive substance consumed in France, with about 15 million regular consumers. The National institute on Alcohol Abuse and Alcoholism (NIAAA) considers alcohol abuse to be more than 14 units of alcohol a week for men and 7 units for women. The specific complication of alcoholism is the alcohol withdrawal syndrome. Its incidence reaches up to 30 % and its main complications are delirium tremens, restlessness, extended hospital stay, higher morbidity, and psychiatric and cognitive impairment. Without appropriate treatment, delirium tremens can lead to death in up to 50 % of patients.

**Methods/design:**

This prospective, double-blind, randomised controlled study versus placebo will be conducted in twelve French intensive care units (ICU). Patients with an alcohol intake level higher than the NIAAA threshold, who are under mechanical ventilation, will be included. The primary objective is to determine whether baclofen is more efficient than placebo in preventing restlessness-related side effects in the ICU. Secondary outcomes include mechanical ventilation duration, length of ICU stay, and cumulative doses of sedatives and painkillers received within 28 days of ICU admission. Restlessness-related side effects in the ICU are defined as unplanned extubation, medical disposal removal (such as urinary catheter, venous or arterial line or surgical drain), falling out of bed, ICU runaway (leaving ICU without physician's approval), immobilisation device removal, self-aggression or aggression towards medical staff. Daily doses of baclofen/placebo will be guided by daily creatinine clearance assessment.

**Discussion:**

Restlessness in alcoholic patients is a life-threatening issue in ICUs. BACLOREA is a randomised study assessing the capacity of baclofen to prevent agitation in mechanically ventilated patients. Enrolment of 314 patients will begin in June 2016 and is expected to end in October 2018.

**Trial registration:**

ClinicalTrials.gov Identifier: NCT02723383, registered on 3 March 2016.

**Electronic supplementary material:**

The online version of this article (doi:10.1186/s13063-016-1539-2) contains supplementary material, which is available to authorized users.

## Background

Alcohol is the leading psychoactive substance consumed in France with about 15 million regular consumers. The ESEMED4 study in 2001 [1] registered psychiatric disorders in about 10 % of men and 2.5 % of women with abusive alcohol intake. In 2013, alcohol was responsible for one death every 12 min in France [2]. In general hospitals, 20 to 35 % of men and 10 % of women suffer from chronic alcoholism [3]. In an intensive care unit (ICU), 28 % of admissions are related to abusive alcohol intake [4]. The National institute on Alcohol Abuse and Alcoholism (NIAAA) considers alcohol abuse to be more than 14 units of alcohol a week for men and 7 units for women.

ICU admission is an independent risk factor for delirium [5–7], pain-related health care issues, sleeping problems and neurological dysfunction [8–10]. The specific complication of alcoholism is alcohol withdrawal syndrome. Its incidence reaches up to 30 % [11] and its main complications are delirium tremens (DTs), restlessness, extended hospital stay, higher morbidity, and psychiatric and cognitive impairment [12–14]. Without appropriate treatment, DTs can lead to death in 50 % of patients [15]. Alcohol abuse leads to specific neurological dysfunction characterised by a fall in neuronal density [16] and consequently a higher risk of convulsion, confusion and restlessness [17]. Moreover, alcoholism also worsens vital prognosis [18, 19] and increases the morbidity and mortality of surgical patients [11, 20].

Alcohol withdrawal syndrome and delirium are commonly encountered in ICUs but standard treatment fails to reduce restlessness and related complications. Agitation related to DTs can lead to unplanned extubation and medical disposal removal and requires deep sedation, increasing the time on the ventilator. The beneficial effects of baclofen in preventing such a condition have never been reported in ICUs for at-risk drinkers.

Baclofen has been commercialised since 1974 and its target is the type-B γ-aminobutyric acid (GABA) receptor. In at-risk patients, this drug can reduce alcohol craving. Randomised studies have reported its efficiency in reducing both alcohol withdrawal syndrome [21, 22] and alcohol intake [23, 24] with conclusive safety data. Doses of up to 400 mg a day are commonly used, with very few side effects, in outpatients with working lives. Sixty to seventy percent of baclofen-treated patients reached total abstinence with a mean daily dose of 147 mg [25]. These data, taken altogether, have led the French medicinal and health products safety agency (ANSM) to advocate new randomised controlled trials to assess both the safety and efficiency of high doses.

Our objective is to take advantage of sedation and mechanical ventilation to allow clinicians to deliver high doses of baclofen without neuropsychiatric side effects for quick and marked effects, in an attempt to control restlessness, craving and related morbidity in ICU.

## Methods/design

### Design

BACLOREA is a prospective, multicentre, double-blind, randomised controlled study versus placebo, performed in at-risk drinkers according to NIAAA criteria. We will assess the superiority of baclofen compared to placebo in preventing restlessness-related complications. The randomisation sequence will be computer-generated and stratified at the 11 participating centres. This study follows the international recommendations for interventional trials (see the SPIRIT checklist in Additional file 1).

### Hypothesis

Early administration of baclofen to at-risk drinkers may reduce restlessness and its related complications when sedation is interrupted. We hypothesise that the administration of baclofen can reduce the incidence of patients who have at least one complication of agitation, including: unplanned extubation, medical disposal removal, falling out of bed, ICU runaway, immobilisation device removal, and self-aggression or aggression toward medical staff from 42 to 27 %.

### Trial intervention

After randomisation, the patients will receive double-blind baclofen or placebo. Daily doses will be adapted to daily modification of the diet in renal disease (MDRD) creatinine clearance from 150 to 50 mg (see Table 1). On the day of randomisation, the patient will receive the full daily dose in a one-shot administration. Then daily doses will be divided into three intakes on the following days. During the mechanical ventilation period, the treatment/placebo will be administered via the nasogastric feeding tube. After extubation, the treatment will be administered either via the nasogastric tube or the oral route. The doses were determined after a preliminary pilot study and previous trial analysis regarding efficiency and safety data [25].

**Table 1 Tab1:** Doses of baclofen or placebo adjusted on daily assessment of the patient’s creatinine clearance

MDRD	D1 Loading dose	D2 and following days until extubation/tracheotomy at D15
Cl ≥90	150 mg	50-50-50
Cl 89–60	100 mg	30-20-50
Cl 30–59	70 mg	20-20-30
Cl <30 or continuous HD	50 mg	20-10-20
IHD	50 mg	50 mg before each session
Cl <15 without HD/IHD	50 mg	No administration

*Cl* renal clearance, *D* day, *HD* haemodialysis, *IHD* intermittent haemodialysis, *MDRD* modification of the diet in renal disease

The treatment will be tapered over a 7-day period after extubation or tracheotomy, or after the 15th day of treatment if the patient is still under mechanical ventilation. Treatment will be interrupted as described in Table 2.

**Table 2 Tab2:** Gradual interruption of baclofen or placebo after extubation or tracheotomy or on the 15th day of treatment

Dose administered on the day of extubation/tracheotomy/15th day	150 mg	100 mg	70 mg	50 mg	IHD 50 mg
Day +1	100 mg (20-30-50)	70 mg (20-20-30)	50 mg (10-20-20)	30 mg (10-10-10)	30 mg before dialysis (no administration if the patient is not dialysed)
Day +2	70 mg (20-20-30)	50 mg (10-20-20)	30 mg (10-10-10)	20 mg (10-0-10)	30 mg before dialysis (no administration if the patient is not dialysed)
Day +3	50 mg (10-20-20)	30 mg (10-10-10)	20 mg (10-0-10)	10 mg (10-0-0)	10 mg before dialysis (no administration if the patient is not dialysed)
Day +4	30 mg (10-10-10)	20 mg (10-0-10)	10 mg (10-0-0)	Stop	Stop
Day +5	20 mg (10-0-10)	10 mg (10-0-0)	Stop		
Day +6	10 mg (10-0-)	Stop			
Day +7	Stop				

*IHD* intermittent haemodialysis

Clinical and biological safety data will be collected throughout the treatment period and the following 10 days, including blood count and liver function tests (see Additional file 2: SPIRIT Figure 3).

### Concomitant medication/treatment

All other interventions will be performed at the discretion of the attending physicians. Participating ICUs will monitor sedation and pain in ventilated patients using specific scales according to international guidelines [26].

### Population

At ICU admission, patients with a mechanical ventilation (MV) duration expected to be equal to or longer than 24 h may be included.

For patients with tracheal intubation at ICU admission:If intubation was performed less than 48 h before admission, inclusion can be performed within 24 h after admissionIf intubation was performed 48 h or more before admission, inclusion cannot be performed

For patients without tracheal intubation at ICU admission:If intubation was performed within the first 48 h after admission, inclusion can be performed in the first 24 h after intubationIf intubation was performed at or after 48 h, inclusion cannot be performed

All patients, whatever the severity of organ failure, would be eligible for screening inclusion.

### Inclusion criteria

Adults aged from 18 to 70 years under mechanical ventilation for *1 day* or more with an estimated alcohol intake of:14 units of alcohol per week during the month before hospitalisation for men aged 18 to 647 units of alcohol per week during the month before hospitalisation for women or men older than 65

### Exclusion criteria

Patients fulfilling one or more of the following criteria will not be included:Baclofen administration before ICU admission (personal treatment or single administration)PregnancyPorphyriaBurn injuries on ICU admissionPersonal treatment including gamma-hydroxybutyric acid (Alcover/Xyrem)Recent stroke or subarachnoid haemorrhage or head trauma with radiological evidenceParaplegia or tetraplegiaCardiac arrest with resuscitation manoeuvres before or after ICU admissionContraindication to enteral drug administrationLack of social protectionHypersensitivity to baclofenCoeliac diseaseRefractory epilepsyDementia, schizophrenia, bipolar disorder or severe depressionParkinson’s diseaseHealth care limitation owing to a poor prognosisTracheotomy on ICU admission

### Randomisation and blinding

The clinicians will perform screening, enrolment and randomisation. Randomisation is centralised, web-based and accessible 24 h a day according to the allocation list on https://www.dirc-hugo-online.org/csonline/. Randomisation will be stratified at the centres using a fixed block size of 1:1 and a randomisation number will be allocated to each patient. Baclofen and placebo will be prepared and ‘blinded’ at Nantes University Hospital pharmacy. The independent trial statistician, patients, clinicians and nurses will be blinded for the allocation of treatment.

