### Protocol suspension and severe adverse reactions

The treatment could be discontinued:Temporarily if:○ Renal clearance falls below 15 ml/min without haemodialysis support○ Liver tests (amino-transferase enzymes) are more than 20 times the normal○ Heart rate falls below 50 BPM with haemodynamic consequencesDefinitively if:○ Allergic symptoms appear○ Heart rate falls below 35 BPM whatever the haemodynamic profile○ Non-reactive uni/bilateral mydriasis develops○ Patient has a seizure in the ICU○ Patient has a stroke in the ICU with computed tomodensitometry (CT) scan confirmation○ Eyes not open 72 h after total sedation is interrupted

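### The protocol states a fixed block within each centre and gives a ratio where the block size belongs; if the blind leaks, later allocations in that centre become partly predictable

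*Protocol article*

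**What the plan says.** The scheme is set out in the protocol article under Randomisation and blinding:

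- Scheme: "Randomisation will be stratified at the centres using a fixed block size of 1:1".
- Who operates it: "The clinicians will perform screening, enrolment and randomisation".
- Concealment: "Randomisation is centralised, web-based and accessible 24 h a day according to the allocation list".
- Study drug: "Baclofen and placebo will be prepared and ‘blinded’ at Nantes University Hospital pharmacy".
- Blinding: "The independent trial statistician, patients, clinicians and nurses will be blinded for the allocation of treatment".

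The Design section adds that the sequence is computer-generated and "stratified at the 11 participating centres" (the abstract says twelve units). No block length in patients is given anywhere in the article.

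Two other places bear on whether the blind could leak. The Background gives the aim as to "take advantage of sedation and mechanical ventilation to allow clinicians to deliver high doses of baclofen without neuropsychiatric side effects". The section on protocol suspension lists, among the reasons for definitive discontinuation, "Eyes not open 72 h after total sedation is interrupted".

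**The concern.** The sentence is faulty on either reading. 1:1 is an allocation ratio, not a block size; if it is read as a size, it means one patient per arm, a block of two, which is the most predictable block there is. On both readings it tells sites that the length is constant.

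With a constant block length, knowing earlier arms in a block shifts the odds for the next patient. The person who could use this is the person enrolling, and several entry decisions need judgement: ventilation expected to last 24 h or more (Population), an estimated alcohol intake (Inclusion criteria), and limitation of care for poor prognosis (Exclusion criteria). A clinician with a view on the next allocation could, even without intending to, enrol or hold back a patient accordingly. That is selection bias, and baseline adjustment cannot be relied on to remove it.

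The route requires the blind to leak first. Dosing starts under sedation but continues until extubation, tracheotomy or day 15 and is then tapered (Trial intervention), so some patients are awake on study drug. Trial status plans two inclusions per unit per month, about one every 15 days, so a team may often have watched one patient wake before it randomises the next.

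**Working it through.** **1. The plan's own figure.** Inputs from Statistics: 42% against 27%, two-sided 5%, power 80%. Mean rate = (0.42 + 0.27)/2 = 0.345.

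n per arm = [1.960 × √(2 × 0.345 × 0.655) + 0.842 × √(0.42 × 0.58 + 0.27 × 0.73)]² / 0.15²
= [1.960 × 0.6723 + 0.842 × 0.6638]² / 0.0225 = 3.521/0.0225 = 156.5, rounded up to 157.

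Total 2 × 157 = 314, as stated. This figure does not depend on the block scheme and serves here only for scale: 314/11 ≈ 29 patients per centre, or 314/12 ≈ 26 with the abstract's count.

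**2. Assumptions.** The article gives no block length, so lengths B = 2, 4, 6 and 8 are assumed. The guesser knows B, predicts the arm that appears to be behind in the current block, and tosses a coin when the arms are level. Earlier arms are recognised with accuracy q. The documents give no value for q, so a range is shown.

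**3. Share of allocations fully determined when q = 100%.** Share = 2/(B + 2).

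| B | Share | Of 314 |
|---|---|---|
| 2 | 50% | 157 |
| 4 | 33% | about 105 |
| 6 | 25% | about 78 |
| 8 | 20% | about 63 |

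**4. Chance that the second patient in a block gets the opposite arm when only the first is known.** (B/2)/(B − 1): 1/1 = 100%, 2/3 = 67%, 3/5 = 60%, 4/7 = 57% for B = 2, 4, 6, 8.

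**5. Correct-guess rate over all patients.** With q = 100%, expected correct guesses per block are B/2 + ½ × [2^B / C(B, B/2) − 1], where C(B, B/2) is the number of balanced blocks:

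- B = 2: 1 + ½(4/2 − 1) = 1.5; 1.5/2 = 75%
- B = 4: 2 + ½(16/6 − 1) = 2.833; 2.833/4 = 71%
- B = 6: 3 + ½(64/20 − 1) = 4.1; 4.1/6 = 68%
- B = 8: 4 + ½(256/70 − 1) = 5.329; 5.329/8 = 67%

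For q below 100% and B = 2, the first guess is right half the time and the second with probability q, so the rate is (0.5 + q)/2; at q = 0.7 this is 60%. Longer blocks were enumerated over all balanced sequences:

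| Recognition of earlier arms | B = 2 | B = 4 | B = 6 | B = 8 |
|---|---|---|---|---|
| 50% (blind intact) | 50% | 50% | 50% | 50% |
| 60% | 55% | 53% | 52% | 52% |
| 70% | 60% | 56% | 55% | 54% |
| 80% | 65% | 60% | 58% | 57% |
| 100% | 75% | 71% | 68% | 67% |

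Fixed blocks alone therefore give nothing away. The added predictability grows with recognition of earlier arms and shrinks with block length.

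**The case against.** Allocation is central, placebo is blinded by a pharmacy, and clinicians and nurses are blinded. A centre sees the order of its patients, not their arms, and the first row of the last table shows that the fixed block then does no harm. This stands, and it makes the concern conditional.

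A reader might infer that baclofen is recognisable at the bedside, or that the sponsor expects slow waking and bradycardia as drug effects. The documents do not say so. Slow waking and low heart rate appear only in a list of reasons to discontinue, beside items such as low renal clearance and confirmed stroke. Patients of any severity may enter and other sedation is left to the attending physician, so neither sign identifies the arm. A leak after sedation stops is plausible, but it is an assumption.

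A reader might also infer that one guessed allocation reveals the next. That holds only for a block of two. For lengths 4, 6 and 8 the odds move to 67%, 60% and 57%, and no length is clearly published. The actual length may be in the full protocol, so its absence from the article is not itself a fault.

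Finally, different co-treatment and biased judgement of bedside events would come mainly from recognising the current patient's arm, which block sizes do not affect. This also stands and limits what the fix can achieve.

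The stated choice of a fixed block and the faulty phrase are untouched by these points.

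**Conclusion.** The point holds as a cheap, conditional improvement to a stated design choice. The sentence needs correcting in any case, because it gives a ratio as a block size and tells sites that the length is constant.

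The size depends on an unknown. With the blind intact the correct-guess rate is 50%. At 70% recognition it is about 60%, 56% and 55% for block lengths 2, 4 and 6. The ceiling of 75%, 71% and 68%, with half, a third and a quarter of allocations determined, needs full recognition of every earlier arm and a block length known to the site; nothing in the documents supports full recognition. The block lengths and recognition rates are assumptions. The consequence at issue is selection bias through discretionary entry; the article does not show that it has occurred or will occur. The sample size of 314 is unaffected.

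**What to change.** Under Randomisation and blinding, replace the phrase on the block size by: 1:1 allocation in permuted blocks of randomly varying size within centre, with sizes held only by the randomisation unit and not disclosed to sites.

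The central web system can carry such a list, preferably from before first enrolment. The change costs one new computer-generated list and one sentence, with no extra patients, visits or staff. The downside is slightly looser balance within a centre at any given time. If the change comes after supplies have been tied to the existing list, some relabelling would be needed; the article does not say whether supplies are tied in this way.

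Varying block sizes limit only the prediction of later allocations. They do not address bias from recognising the current patient's own arm.

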### Primary outcome measure

Composite score: occurrence (yes or no) of agitation-related adverse events during treatment/placebo administration with at least one sign out of the following:Unplanned extubationMedical disposal removalFalling out of bedICU runawayImmobilisation device removalSelf-aggression or aggression towards medical staff

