### Statistics

We hypothesised that baclofen administration can reduce the incidence of patients with at least one complication of agitation, using a two-sided test with an α of 5 % and 80 % power, from 42 to 27 %. This hypothesis in the placebo group is based on personal data. As a result, 314 patients are needed. Our study will include patients whatever their severity. Some patients may die before sedation interruption thus altering the power of the study. We therefore plan an interim analysis (after 50 % of inclusions), to adjust the sample size to maintain the statistical power. Friede and Kieser’s method [27, 28] allows both the initial hypothesis and the type-1 error planned a priori to be maintained. The analysis will be stratified at the participating centres. Statistical analysis will take place on an intention-to-treat principle. For the primary outcome, a logistic regression model will be applied to compare the proportion of agitation between the two treatment arms. Two sensitivity analyses will be performed and will consider dead patients to be without agitation, or as patients with or without agitation. A per-protocol analysis will also be performed to exclude patients with any of the exclusion criteria or without the inclusion criteria, or patients with incomplete treatment administration.

For the secondary outcomes, a Poisson regression model will be applied to compare the number of adverse events related to agitation, between the two treatment arms. Both length of ICU stay and mechanical ventilation will be compared with a log-rank test. Logistic regression will be used to compare binary qualitative secondary endpoints.

Normally distributed variables will be expressed as mean and standard deviation; nonnormally distributed variables will be expressed as median and interquartile range. Categorical variables will be expressed as numbers and percentages.

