## Discussion

Restlessness in alcoholic patients is a life-threatening issue in ICUs. Baclofen usefullness was already reported to treat alcohol withdrawal syndrome, that's why its accuracy in ICU had to be assessed by large multicentre studies. Invasive Mechanical ventilation and continuous tight monitoring will allowed to introduce relatively high doses of Baclofen to reach fast effective plasma drug concentration and ensure patient security. In parallel, reducing agitation may avoid other hypnotic drugs administration and so reduce their side effects: Mechanical ventilation duration and its complications, delirium and neuro-psychiatric aftereffects.

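### The primary outcome counts a patient who stays unarousable after sedation stops as event-free, and no listed outcome or sensitivity analysis addresses delayed awakening

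*Protocol article*

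**What the plan says.** The Primary outcome measure section of the protocol article defines the endpoint as "Composite score: occurrence (yes or no) of agitation-related adverse events during treatment/placebo administration with at least one sign out of the following". Six signs follow: unplanned extubation, removal of a medical device, a fall from bed, leaving the unit, removal of an immobilisation device, and aggression. No condition requires the patient to be awake or off sedation.

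The Hypothesis section places the expected benefit at awakening: early baclofen "may reduce restlessness and its related complications when sedation is interrupted". The Background states the aim of giving high doses under cover of sedation and ventilation.

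Under Protocol suspension and severe adverse reactions, one ground for stopping study treatment definitively is "Eyes not open 72 h after total sedation is interrupted".

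The Secondary outcome measure section has sixteen entries. They include the Riker Sedation Agitation Scale (SAS), total sedative and painkiller doses, ventilation duration, ventilation-free days, ICU stay, tracheotomy for weaning failure, mortality, and agitation events within 28 days of ICU admission. None is awakening, time to awakening, or persistent unresponsiveness.

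The Statistics section plans two sensitivity analyses of the primary outcome. Both concern how patients who die are classified.

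**The concern.** The endpoint records the absence of events. That absence has two quite different causes: the patient is awake and calm, or the patient cannot move enough to have an event. The trial hypothesis is about the first. If study drug prolongs unresponsiveness after other sedation stops, the second also lowers the event rate in the baclofen arm, and the primary analysis counts it as benefit. Blinding and intention-to-treat do not protect against this, because the effect acts through the drug on the patient's capacity to have an event.

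The protocol already recognises the same problem for death. It notes that some patients may die before sedation is interrupted, adds a secondary composite with 28-day mortality, and plans sensitivity analyses for deaths. Non-awakening also prevents events and is plausibly related to the drug, but it has no counterpart in the plan.

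The event window adds to this. Events count only during treatment administration. Read literally, definitive discontinuation for non-awakening also closes the period in which that patient's events can count.

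**Working it through.** **1. The plan's own figure.** Inputs from the Statistics section: "using a two-sided test with an α of 5 % and 80 % power, from 42 to 27"%, with 1:1 allocation (Randomisation and blinding). With the pooled-variance formula and no continuity correction:

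- mean rate = (0.42 + 0.27)/2 = 0.345
- n per arm = [1.960·√(2·0.345·0.655) + 0.842·√(0.42·0.58 + 0.27·0.73)]² / 0.15² = (1.318 + 0.559)² / 0.0225, which rounds up to 157
- total = 2 × 157 = 314, power 80.1%

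This matches "As a result, 314 patients are needed". The sample size is not in dispute; 157 per arm is carried forward.

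**2. How each patient state is scored under the text.**

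| State after sedation stops | Primary outcome | Provision elsewhere in the plan |
|---|---|---|
| Awake, calm | no event | none needed |
| Awake, agitated, with a listed sign | event | none needed |
| Unarousable at 72 h | no event | ground for definitive discontinuation; no outcome, no sensitivity analysis |
| Dead | not fixed by the outcome definition | two sensitivity analyses and a secondary composite with 28-day mortality |

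**3. Illustration of size.** The documents give no rate of non-awakening, so the share s is an assumption. Suppose baclofen has no effect on agitation, the event risk is 42% in anyone able to have an event, all placebo patients can have one, and an extra share s of the baclofen arm cannot have one at any time in the window. Then:

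- baclofen rate = 0.42 × (1 − s)
- spurious difference = 0.42 × s
- SE = √{[0.42·0.58 + p(1 − p)]/157}, where p is the baclofen rate
- chance of a significant result favouring baclofen ≈ P(Z > 1.96 − difference/SE)

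| s | Baclofen rate | Spurious difference | Share of the planned 15 points | SE | Chance of false benefit |
|---|---|---|---|---|---|
| 0 | 42.0% | 0 | 0 | – | 2.5% |
| 5% | 39.9% | 2.1 points | 14% | 0.0555 | about 6% |
| 10% | 37.8% | 4.2 points | 28% | 0.0552 | about 12% |
| 15% | 35.7% | 6.3 points | 42% | 0.0549 | about 21% |

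To produce the whole planned effect this way, s would have to be 1 − 0.27/0.42 = 35.7%, about 56 of 157 patients.

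**4. What a composite with non-awakening would show in the same scenario.** The baclofen rate becomes 0.42 × (1 − s) + s: 44.9% at s = 5%, 47.8% at 10%, and 50.7% at 15%, against 42% on placebo. The sign reverses, so the analysis can tell the two explanations apart.

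**The case against.** The strongest reply is that over-sedation would not go unseen. The Riker SAS grades sedation as well as agitation, and the Concomitant medication/treatment section has participating units monitor sedation with specific scales. Ventilation duration, ventilation-free days, ICU stay, tracheotomy and mortality should all differ between unarousable and calm patients. Agitation events are also counted to day 28, so a patient who wakes late can still contribute one. Clinical safety data are collected during treatment and for 10 days after. Tabulating discontinuation reasons by arm is commonly left to the full protocol or analysis plan.

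Much of this stands. A reader might infer that a positive primary result could not be separated from over-sedation at all; the listed outcomes do not support that. What remains is narrower. None of these measures is anchored to the moment sedation stops, so SAS alone does not separate clinician-given sedation from a study-drug effect. The day-28 event outcome still scores a patient who never wakes as event-free. Nothing links any of these measures to the reading of the primary result. The article does state its outcomes and its sensitivity analyses of the primary, and there only death is treated as a state that prevents events.

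Two further inferences are tempting and unsupported. The first is that the net bias must favour baclofen. Over-sedation by study drug would, but other sedation is at the physicians' discretion, and heavier sedation on placebo would suppress events there. The second is that the Discussion names unarousability as a harm the trial seeks to reduce. Its statement that "reducing agitation may avoid other hypnotic drugs administration and so reduce their side effects" concerns other hypnotics, and the effects it lists are ventilation duration and its complications, delirium and neuropsychiatric after-effects.

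The illustration also leans high for a given s: it allows no late waking within the window and assumes every placebo patient can have an event, although the Statistics section expects deaths before sedation interruption.

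**Conclusion.** The point holds in a limited form. As written, the primary outcome credits persistent unresponsiveness as success, the protocol regards that same state as grave enough to end treatment, and no outcome or sensitivity analysis of the primary takes it up. Part of an apparent benefit could therefore reflect over-sedation, and the partial safeguards are not set up to say how much.

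The size is unknown. The 6 to 21% chance of a false benefit depends wholly on an assumed 5 to 15% excess of non-waking patients and on the simplifications in the working. It shows how sensitive the endpoint is, not how likely the problem is. The finding is not an internal contradiction, leaves the 314 patients untouched, and implies no view on the dose or the stopping criterion. It is a gap that is cheap to close before unblinding; added afterwards, the same analysis would be post hoc.

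**What to change.** (a) Report by arm, as a prespecified secondary or safety outcome, non-awakening by the 72 h criterion already in the protocol. The denominator should be patients whose sedation was interrupted, with deaths before interruption shown separately by arm, because the outcome is undefined for them.

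(b) Add to the Statistics section a prespecified sensitivity analysis of the primary outcome in which an agitation-related event or non-awakening by that criterion counts as failure. Read it alongside the primary result and the SAS. A rule making the trial's claim conditional on this analysis is not needed.

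Cost: recording the times of sedation stop and eye opening in the case report form, plus one more supporting analysis. The criterion already has to be assessed at the bedside, and no extra patients are required. The downside is a supporting estimate that may be less favourable and that also counts non-awakening from causes other than study drug, so it should be presented as a check and not as a replacement for the primary analysis.
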